### Exclusion period and participation in another study

The exclusion period defined in the setting of this study is 3 months, period during which the subject cannot participate in another clinical research study.

This exclusion is justified to prevent any risk of interference in interpretation of results.

The investigator makes certain that persons who may be subjects in the biomedical research study are not already participating in another study which may make their inclusion in the proposed study impossible. He/she also makes certain that they have not participated in a study for which currently an exclusion period is required, in particular, using the National File of persons who are subjects in biomedical research studies.

# Practical conduct of study

## Detailed description of procedures practiced on persons:

So-called screening/inclusion visit D-14 to D-1

- Information of the person who is a subject in the study and collection of his or her consent
- Medical visit and nutritional evaluation
- Laboratory test evaluation specific for inclusion consisting of:
  - complete blood count with white blood cell differential count (CBC-) and erythrocyte sedimentation rate (ESR),
  - HIV and HCV serologies,
  - renal function tests (serum electrolytes (plasma sodium, plasma potassium, calcium, alkaline reserve, serum phosphorus), creatinine, blood urea nitrogen)
  - liver function tests (ALT, AST, Gamma GT)
  - lipid parameter profile (Total cholesterol, HDL and LDL cholesterol, triglycerides)
  - glycaemia
  - a pregnancy test if a female volunteer is not post-menopausal and not using an effective method of contraception
  - nutritional diary (see appendix 7)

Visit V2-D0 -randomisation:

- Verification of criteria for inclusion
- Clinical examination, somatic and nutritional evaluation (blood pressure, weight, waistline, anthropometric measurements including body composition, nutritional diary)
- Laboratory test evaluation after an overnight fast of 8 hours, and including measurement of glycaemia, serum insulin, total cholesterol, LDL-, HDL-, triglycerides, CRPus, IL6, serum leptin, HbA1c
- Needle aspiration of subcutaneous adipose tissue
- Distribution of a nutritional diary and of an operational diary for the next visit
- Distribution and retrieval of quality of life questionnaires TFEQ*, physical activity questionnaires (see appendix 6) and nutritional diary (appendix 7)
- Distribution of treatment (Glycabiane)
- Measurement of body composition (DEXA)
- Setting of an appointment for visit 3 (D60±7)

*The Three Factor Eating Questionnaire (TFEQ) is a self-questionnaire which makes it possible to study three dimensions of dietary behaviour: hunger, restriction and disinhibition. It is defined by occurrence of uncontrolled access of hyperphagia, which most often are subsequent to lifting of dietary restrictions.

Visit 3 (V3 at month 2) at D 60 ± 7

- Clinical examination, somatic and nutritional evaluation (blood pressure, weight, waistline, anthropometric measurements, nutritional diary)
- Recovery of empty boxes and blisters of products consumed
- Setting of an appointment for end of supplementation visit (D120±7)

Visit 4 (V4 at month 4) at end of supplementation at D 120 ± 7

- Recovery of empty boxes and blisters of products consumed and of remaining products not consumed
- Distribution of nutritional diary and of operating diary for next visit
- Distribution and recovery of quality of life questionnaires, physical activity questionnaire and nutritional diary (appendix 7)
- Clinical examination, somatic and nutritional evaluation (blood pressure, weight, waistline, anthropometric measurements, nutritional diary)
- Laboratory test evaluation after an overnight fast of 8 hours, and including glycaemia, serum insulin, total cholesterol, LDL-, HDL-, triglycerides, CRPus, IL6, serum leptin, HbA1c
- Needle aspiration of subcutaneous adipose tissue
- Measurement of body composition (DEXA)
- Setting of an appointment for the follow-up visit (D194± 7)

Visit 5 (V5-at month 6) of follow-up at D 194 ± 7

- Clinical examination, somatic and nutritional evaluation (blood pressure, weight, waistline, anthropometric measurements, nutritional diary)
- Laboratory test evaluation after an overnight fast of 8 hours, and including glycaemia, serum insulin, total cholesterol, LDL-, HDL-, triglycerides, CRPus, IL6, serum leptin, HbA1c
- Collection of nutritional diary and of operating diary
- Distribution and recovery of quality of life questionnaires
- End of study

**Nutritional and inflammatory evaluation**

We are going to characterise the lipid profile and glycaemic control of subject: before and after each period. At start and at end of each period, after overnight fasting for 8 hours and blood sample will be collected from the subject fasting (for measurement of glycaemia, serum insulin, total cholesterol, LDL, HDL, triglycerides, leptin, and adiponectin). Inflammatory factors: CRPus and IL6 will be measured (ELISA).

Fatty mass and its distribution will be measured with dual energy X-ray absorptiometry (DEXA). A sample of abdominal subcutaneous adipose tissue collected by needle puncture will be performed by suctioning under a vacuum after local anaesthesia with 10% xylocaine without isoprenaline.

We are going to characterise the dietary profile throughout the study using the nutritional diary, of a “weekly” type over 3 days.

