## Expected benefits and/or foreseeable risks for persons

Participation in this study can lead to progression of knowledge by physicians on understanding the prevention of diabetes and elevation of glycaemia, but the benefit for participating subjects cannot be evaluated precisely, since this is the subject of the study. Current knowledge makes it possible to formulate the hypothesis of the utility of Glycabiane in terms of regulation of fasting glycaemia in prediabetic subjects who ingest Glycabiane and thus limit the progression to type 2 diabetes (with micro and macrovascular complications). In the exceptional case where, for a given subject, the study might demonstrate a risk to health, appropriate data would be communicated to the investigator who would provide them in a relevant manner to the person concerned, in the setting of respect for persons and medical secrecy.

- **Risks related to treatments**

The studied product is a dietary supplement which comes in capsule form containing cinnamon extract, carnosine and chromium. It is already marketed under the trade name Glycabiane by PiLeJe since 2008.

Since 2010, when the collection of adverse events related to ingestion of the product was set up, nutrition vigilance has not recorded any unexpected serious adverse event and has been informed of only a single case of an adverse event whose causal relation with the product was doubtful.

- No cases in 2010
- 1 case in 2011: gastric burning (causal relationship: doubtful)
- No cases in 2012
- **Risks related to metabolic investigations.**

***Suctioning of adipose tissue by needle puncture:*** This procedure was performed under local anaesthesia, with the possible unpleasant effect being an ecchymosis generally of small size which is reabsorbed in a few days, and, in rare cases, a small haematoma (small collection of blood), reabsorbed in a few days and that can require application of an alcohol dressing. The dose used for local anaesthesia (Xylocaine 1% without adrenaline) is non-toxic and very rarely allergenic (amino amide allergy)

****DEXA:*** It is hazardless and provides radiation of about 70-140 kV (less than one chest X-ray). The examination lasts about ten minutes.

- Study constraints.

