**Sampling of adipose tissue:**

Samples of adipose tissue under the abdominal skin (about 500 mg) will be collected by needle puncture at time of inclusion and after follow-up. This sample, collected by the investigator, is performed in routine practice in the department of nutrition of Pitié Salpetrière Hospital. After local anaesthesia (1% Xylocaine without adrenaline), suctioning of adipose tissue with a very small calibre needle is performed. Part of the sample will make it possible to measure adipocyte size before and after supplementation. Another will be used to evaluate:

1) the inflammatory status of adipose tissue with a ELISA assay measurement of cytokine IL-6 and of adipokine, adiponectin.

2) sensitivity to insulin by study of phosphorylation Akt by Western Blot technique and by secretion of adiponectin.

These analyses 1) and 2) will be subcontracted to AdipoPhYt firm.

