A sample of adipose tissue of about 500 mg will be collected by needle puncture suctioning performed on volunteers. This sample, collected by the investigator, is performed in routine practice in the department of nutrition of Pitié Salpetrière Hospital to measure cell size. After local anaesthesia with 2 ml of 1% xylocaine without isoprenaline, the peri-umbilical adipose tissue will be collected by a small calibre needle with suctioning to follow the outcome of the population and morphology. For each adipose tissue sample collected (subcutaneous), cell size will be evaluated before and after treatment.

Investigational studies for investigation of adipose tissue (inflammatory status, insulin sensitivity) in vitro in culture will be performed by the AdipoPhyt firm.

- Specific instructions during the investigational period

Persons who are subjects in the study must not change their dietary habits. Lastly, any form of medical therapy initiated during the investigational period must be reported by the volunteer.

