# Collection of human biological samples

- Description of type of samples:

Blood samples and adipose tissue.

- Description of conditions for sampling:

Blood samples will be collected at D-1 to -14, D0, D 120 and D180 after 8 hours of fasting, between 8 and 9:30 am. Test tubes collected will be kept at 4 °C starting with collection of the sample, centrifuged to 4 °C, divided into aliquots and stored at -80 °C until their use for the planned analyses.

The sample of adipose tissue will be collected after application of local anaesthesia with 2 ml of 1% xylocaine without isoprenaline, peri-umbilical adipose tissue sample will be collected by suctioning with a fine needle to measure the adipocyte size immediately and to conduct study of cell culture in vitro.

Blood samples will be stored by INSERM U872 (Eq7) at -80 °C up until end of study (last analysis of last patient included), and then they will be destroyed. Those of peri-umbilical adipose tissue will be stored at -80 °C by ADIPOPHYT up until end of study (last analysis of last patient included), and then they will be destroyed.

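### The protocol gives two concentrations, ten-fold apart, for the local anaesthetic used in the fat aspiration, and assesses the risk of only one

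*Protocol*

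**What the plan says.** Five places in the protocol describe the anaesthesia for the abdominal subcutaneous fat aspiration.

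- **Section VII.A, Nutritional and inflammatory evaluation:** the sample is taken "after local anaesthesia with 10% xylocaine without isoprenaline". No volume is given.
- **Section VII.A, Sampling of adipose tissue (the next subsection):** "After local anaesthesia (1% Xylocaine without adrenaline". No volume is given.
- **Section IX, Medical devices, peri-umbilical adipose tissue:** "After local anaesthesia with 2 ml of 1% xylocaine without isoprenaline".
- **Section X, Collection of human biological samples:** "local anaesthesia with 2 ml of 1% xylocaine without isoprenaline".
- **Section I.D, Expected benefits and/or foreseeable risks:** "The dose used for local anaesthesia (Xylocaine 1% without adrenaline) is non-toxic and very rarely allergenic".

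The visit descriptions in VII.A schedule the aspiration at V2 (D0) and V4 (D120) and do not restrict it to a subset of subjects. Contraindication to xylocaine as a local anaesthetic is an exclusion criterion in VI.A.2.

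**The concern.** One procedure, on the same tissue in the same subjects, is described with two concentrations of the anaesthetic. Both stand in current operative text, and two of the conflicting descriptions are in consecutive subsections of VII.A. A member of staff who follows the first would use a preparation for which the protocol contains no risk statement, because the reassurance in I.D is tied explicitly to 1%.

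The protocol's own safety and quality machinery also depends on a single description:

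- **Expectedness:** under XI.A, whether an adverse event is unexpected is judged against the information in the protocol or investigator brochure, including information on the procedures performed. With two concentrations, an event related to the anaesthetic has no single reference in the protocol.
- **Monitoring:** under XIX.C the clinical research associate checks compliance with the protocol's procedures. Either concentration complies with one part of the text and deviates from another.
- **Oversight:** XI.E dispenses with a monitoring committee on grounds that concern only the supplement's ingredients. The invasive procedure is not considered there.

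The additive is also worded in two ways, without isoprenaline in some places and without adrenaline in others. This is a lesser point.

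**Working it through.** No sample-size, power or alpha calculation bears on this point. The check is a comparison of texts plus simple arithmetic.

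**Step 1: set the texts side by side.**

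| Place in protocol | Concentration | Volume | Additive stated absent |
| --- | --- | --- | --- |
| VII.A, Nutritional and inflammatory evaluation | 10% | not given | isoprenaline |
| VII.A, Sampling of adipose tissue | 1% | not given | adrenaline |
| IX, peri-umbilical adipose tissue | 1% | 2 ml | isoprenaline |
| X, Collection of human biological samples | 1% | 2 ml | isoprenaline |
| I.D, Risks related to metabolic investigations | 1% | not given | adrenaline |

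The count is one place with 10% against four with 1%.

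**Step 2: look for an explanation in the text.** All five concern needle aspiration of abdominal subcutaneous (peri-umbilical) fat under local anaesthesia. None mentions a second anaesthetic step, a second formulation or a second site. The 10% sentence is neither struck out nor part of a change log.

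**Step 3: size of the discrepancy.** Ratio of concentrations = 10% / 1% = 10. This follows from the documents with no further assumption.

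**Step 4: illustration in milligrams.** Two assumptions are needed: the percentages are weight per volume (10% = 100 mg/ml, 1% = 10 mg/ml), and the 2 ml of sections IX and X also applies to the 10% text.

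- 1%: 2 ml × 10 mg/ml = 20 mg
- 10%: 2 ml × 100 mg/ml = 200 mg
- Ratio: 200 / 20 = 10

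**Step 5: procedures affected.** There are two aspirations per subject. With the 50 subjects to be followed, this gives 50 × 2 = 100 procedures. With the 60 subjects to be selected, the ceiling is 60 × 2 = 120. The ceiling would be reached only if all 60 were randomised and completed V4, whereas VI.A.3 selects 60 so as to follow 50.

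**Step 6: additive wording.** The additive does not track the concentration: the 1% text appears with both wordings, and the 10% text shares its wording with sections IX and X. A preparation free of both additives would satisfy every sentence. This is therefore an inconsistency of wording and does not by itself show that two products are meant.

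**The case against.** The strongest case on the other side is that this is one stray sentence with little practical risk. The trial has a single centre, the investigator takes the sample, and the protocol calls the sampling routine practice in that department. The three subsections that deal specifically with fat sampling or biological samples all agree with one another and with the risk text, and subjects with a contraindication to xylocaine are excluded. On that view, exposure of every subject to the discrepant concentration is a worst case and not an expectation.

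Two further points are fair. The 10% sentence states no volume, so it implies no particular dose, and 200 mg against 20 mg is an illustration. The two additive wordings can both be true of one product.

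What stands of this: the firm figure is a ten-fold ratio of concentrations, not of doses; the milligram figures are conditional; the additive point is secondary; and the single-centre setting probably lowers the chance that the sentence is acted on. None of it removes the contradiction from the governing document. Familiarity at the site is not a control that the protocol specifies, and a majority of four texts to one does not establish which value was intended.

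**Conclusion.** The concern holds. The protocol contradicts itself by a factor of 10 on the concentration of a local anaesthetic for an invasive research procedure scheduled twice per subject, and its risk statement covers only one of the two concentrations. The contradiction and the factor of 10 rest on the text alone. A ten-fold difference in dose (200 mg against 20 mg) would follow only if the volume were the same 2 ml in both cases and the percentages were weight per volume. How many procedures would follow either text cannot be known from the document; about 100 are planned.

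The correction must be made because the matter is one of subject safety and of a single reference for judging adverse events and deviations. It has no bearing on the primary endpoint, the sample size or the analysis. Nothing here implies that either concentration is the right one.

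**What to change.** The sponsor and the responsible clinician should reconcile section I.D, both VII.A subsections, section IX and section X to one statement of concentration, volume and additive. It is best given once, with the other sections referring to it. They should then:

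1. confirm that the risk statement in I.D was made for the preparation settled on, and revise it if it was not;
2. check the information letter (Appendix 1) for the same point;
3. classify the change as substantial or not, as section XVII requires;
4. issue a notice to the site before the first procedure, or before the next one if procedures have begun, and in that case establish from the records which preparation has been used.

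The choice of value is a clinical matter for those responsible and is not proposed here. The cost is a one-line protocol correction and a site notice, plus whatever submission the classification under section XVII entails. Data collection and analysis do not change.

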**Sampling of adipose tissue:**

Samples of adipose tissue under the abdominal skin (about 500 mg) will be collected by needle puncture at time of inclusion and after follow-up. This sample, collected by the investigator, is performed in routine practice in the department of nutrition of Pitié Salpetrière Hospital. After local anaesthesia (1% Xylocaine without adrenaline), suctioning of adipose tissue with a very small calibre needle is performed. Part of the sample will make it possible to measure adipocyte size before and after supplementation. Another will be used to evaluate:

1) the inflammatory status of adipose tissue with a ELISA assay measurement of cytokine IL-6 and of adipokine, adiponectin.

2) sensitivity to insulin by study of phosphorylation Akt by Western Blot technique and by secretion of adiponectin.

These analyses 1) and 2) will be subcontracted to AdipoPhYt firm.

**Processing of biological samples**

All sera intended for measurements of signs of adiposity and inflammatory factors will be analysed in the INSERM Unit U872 (Eq 7). The serum collection will be stored by the Inserm Unit U872 (Eq. 7). For each sample of adipose tissue (subcutaneous) the cell size will be evaluated before and after treatment. Investigational studies of adipose in vitro in culture (inflammatory status and sensitivity to insulin) will be performed by AdipoPhYt.

## Description of general logistical organisation of study

Investigators in the INSERM laboratory U872 (Eq 7), Endocrinology unit, CRNH-Metropolitan Paris in Pitié Salpêtrière will be responsible for recruiting (subcontracted to AdipoPhYt) and selection of patients, dispensing of products, measurement and recording in the case report forms of evaluation criteria.

PiLeJe will provide the product (placebo and active product). A clinical research associate (CRA) from the sponsor will perform monitoring of the study to verify source data and conduct of the study according to good clinical practice. Staff from AdipoPhYt will contact the subject the night before the procedure to remind him or her of the appointment and the requirement to maintain fasting for 8 hours.

INSERM laboratory U872 (Eq 7) is in charge of writing statistical chapters of the protocol, data management, statistical analysis and of writing of the statistical report.

Products and placebo will be blinded by the sponsor (Laboratoire Pileje)

## Provisional study schedule (Flow-Chart)

- Duration of inclusion period: 6 months

In case of withdrawals from study for medical intercurrent reason, subject withdrawn will not replaced

- Total study duration: 24 months
- Total duration of participation of each subject will be 194 consecutive days.

# Studied product

## Description of the studied product

### Glycabiane

- - Medicinal product: a dietary supplement
  - Active substances: OPC-A cinnamon, guanylor chromium and carnosine
  - Pharmaceutical formulation: capsules
  - Composition: one capsule of 595 mg of Glycabiane contains:

| **components** | **Quantity/capsule** |
| --- | --- |
| Cinnamon extract | 228.000 mg |
| Calcium carbonate | 136.750 mg |
| L-carnosine | 100.000 mg |
| Transparent HPMC capsules (size 0) | 95.000 mg |
| Silica (SIPERNAT) | 16.000 mg |
| Talc | 7.000 mg |
| Magnesium stearate | 6.000 mg |
| Silica hydrate | 5.000 mg |
| Guanylor chromium | 1.250 mg |
|  |  |
| **TOTAL** | 595 mg |

In blue, active substances

- Method of administration: oral route
- Dosage: 2 capsules per day to be taken during the noon time meal during 4 months
- Packaging: blisters of 20 capsules
- Labelling: in compliance with decision of 24 May 2006 (Official Journal of 30 May 2006 – text no. 41) setting content of labelling of investigational medicinal products.

### Placebo

- - Medicinal product: placebo
  - Pharmaceutical formulation: capsules
  - Composition: one capsule of 496 mg of Placebo contains:

| Components | Quantity/capsule |
| --- | --- |
| Calcium carbonate | 136.750 mg |
| Transparent HPMC capsule (size 0) | 95.000 mg |
| Talc | 7.000 mg |
| Magnesium stearate | 6.000 mg |
| Silica hydrate | 5.000 mg |
| Silicium dioxide | 16.000 mg |
| Microcrystalline cellulose | 230.25 mg |
|  |  |
| TOTAL | **496 mg** |

- Method of administration: oral route
- Dosage: 2 capsules per day to be taken during the noon time meal during 4 months
- Packaging: blisters of 20 capsules
- Labelling: in compliance with decision of 24 May 2006 (Official Journal of 30 May 2006 – text no. 41) setting content of labelling of investigational medicinal products.

## Dispensing and compliance

The studied product and placebo will be delivered directly to the INSERM laboratory U872 (Eq7).

Temperature for storage of products must be below 25 °C.

Unused products will be recovered and collected by the sponsor who agrees to eliminate waste products in compliance with regulations in force.

Documents describing handling for elimination of waste products (forms for monitoring of waste products, vouchers for collection, etc.) will be issued by the sponsor.

Compliance will be evaluated by means of 2 parameters:

- the patient “interview”;
- the return of unused products;

No medicinal product or treatment that may have an action on glycaemic control in persons who are subjects in the biomedical research will be authorised during the trial.

